### *Side Effects of AZM*

At the recommended doses for nonmycobacterial infections AZM has been generally well tolerated in clinical trials with less than 1% of reactions being described as severe. The most common side effects (1-10%) were diarrhoea, abdominal pain, nausea and vomiting. Metabolic side effects including increases in ALT, AST and alkaline phosphatase were noted in some participants (MIMS). No studies have been carried out on pregnant women, but animal studies suggest that azithromycin is not fetotoxic or teratogenic at doses of up to 200mg/kg/day.

Electrolytes and liver function tests (LFTs) will be done at the initial visit and at each monthly visit during treatment. A rise in the electrolytes or LFTs will result in the test being repeated in one week, if the abnormality worsens the drug will be ceased. If the change is stable a clinical decision will be made to either continue or cease the medication. A record of potential symptoms will be recorded during the regular phone interview.

### **Evaluation of the Study**

The primary outcomes will be:

- Decrease in sputum IL-8

Secondary outcomes will be:

- Decreased in airway bacterial load
- Decreased sputum neutrophils
- Decrease in bronchial wall thickening on chest CT scan
- Number of exacerbations during follow-up

### **Study Schedule (Appendix I)**

#### Run-in period (Visit 1)

Informed consent will be obtained. Participants will be assigned a screening number and their inflammatory subtype determined using induced sputum. A clinical history will be taken that will include the documentation of medication use and an allergy history. Immediate skin

prick testing will be conducted to a range of allergens in participants where this has not been done in the past 12 months. Spirometry will be performed. Sputum will be induced and analysis performed for total cell count and differential. Participants will then enter a 2-week run in phase, during which they will record respiratory symptoms and medication use in a diary (Appendix II). Ex-smokers will be need to have a carbon monoxide diffusion breathing test if one has not been performed in the previous 2 years.

#### Randomisation Visit (Visit 2)

At the conclusion of the run-in period (2 weeks) participants will attend for repeat sputum induction and clinical assessment. Stable participants with neutrophilic airway disease will then be randomised to receive either azithromycin 250mg daily or placebo; both the investigator and participants will be blinded. This will be continued for 12 weeks. Participants will be contacted two weeks after each visit by phone and their respiratory symptoms assessed, medications reviewed, and potential side effects recorded. Electrolytes and liver function tests will be done at visit 2, and then at each visit. Sputum will be collected for a total and differential cell count and bacterial culture. Blood will be collected and stored for assessment of systemic inflammation and inflammatory gene profiling. A Full blood count, electrolytes and liver function tests will be done at visit 2, and then at each visit. A high resolution CT scan of the chest will be formed in a sub-group of participants to assess bronchial wall thickening.

#### Treatment Visits (Visit 3 -5)

The participants will be reviewed after each 4 week period of treatment. Symptom scores, spirometry, sputum induction and analysis and blood parameters will be repeated. At the end of the 12-week treatment phase (visit 4) the medication will be ceased.

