inflammatory effect of AZM on airway inflammation. The primary outcome of this trial will be reduced levels of IL-8 in sputum, however other outcomes will also be assessed such as neutrophil numbers (%), sputum bacterial load (colony forming units/mL), levels of neutrophil elastase. Clinical outcomes will also be determined including symptoms, lung function and quality of life (St George's Respiratory Questionnaire) and severe exacerbations. Participants will be recruited to attend a screening visit, and if stable, they will enter a 2-week run-in period and then be randomised to either AZM (250mg) or placebo daily for twelve weeks. Study visits will occur at monthly intervals where symptoms, lung function and induced sputum will be assessed. A post treatment visit will be conducted 4 weeks after the end of treatment and then we will contact participants by telephone to monitor their airways disease and see if they have had an increase in their symptoms or medication use (exacerbation). We will monitor patients symptoms and medication use for a total of 6 months from their enrolment in the study.

*Sample size* - In a recent study, the effect of clarithromycin in COPD (10) was found to reduce sputum IL-8 levels from 1606 (367) to 882 (144) pg/mL. We will recruit 40 participants (this includes a 10% withdrawal rate) which will give sufficient power (80%) to detect a change in IL-8 levels in the order of 250pg/mL (alpha 0.05).

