### *Patient Allocation*

Patients will be randomly allocated to either receive placebo or AZM 250mg daily. They will take the medication for twelve weeks. Both the participant and the investigators will be blinded to the intervention until the conclusion of the trial. The placebo and agent will be packaged similarly and have identical taste. The use of other medications will be assessed at the commencement of the trial and updated with each contact. The patient will be asked about all new medications commenced and changes in the use of regular medications. If a participant commences treatment with other antibiotic agents during the study they will be withdrawn from the study. To aid compliance medication will be dispensed at each visit. Participants will also be questioned about compliance during the regular phone review.

Treatment will be randomised using random permuted blocks of 6. The data manager in the respiratory research unit using the Randomisation Generator Software (11) will generate the randomisation allocations. The randomisation tables for each stratification list will be

provided to the pharmacy department who will dispense active or placebo medication according to the schedule. The investigator and research team working with the participants will not have access to the randomisation schedule during the study.

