#### End of Treatment Visit (Visit 6)

Symptom scores and quality of life scores will be reassessed. Spirometry, sputum analysis and blood parameters will be repeated. A high resolution CT scan of the chest will be formed to assess bronchial wall thickening.

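### Two visit labels contradict the 12-week treatment phase: the cessation instruction names Visit 4 (week 8 by the protocol's own calendar), and Visit 6 (week 16) is headed end of treatment

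*Protocol*

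**What the plan says.** **Duration.** The Introduction gives twelve weeks of daily treatment. Patient Allocation agrees: "They will take the medication for twelve weeks". So does Randomisation Visit (Visit 2): "This will be continued for 12 weeks".

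**Start.** Visit 2 is the randomisation visit: "At the conclusion of the run-in period (2 weeks) participants will attend for repeat sputum induction and clinical assessment". Stable participants are then randomised and treatment begins.

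**Treatment visits.** The heading "Treatment Visits (Visit 3 -5" covers three visits, and the text below it gives their spacing: "The participants will be reviewed after each 4 week period of treatment". The same section then gives the cessation instruction: "At the end of the 12-week treatment phase (visit 4) the medication will be ceased".

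**Visit 6.** The next section is headed "End of Treatment Visit (Visit 6", with the bracket closing after the number. It lists symptom and quality-of-life scores, spirometry, sputum, blood and a chest CT. It does not say whether drug is being taken up to that visit.

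**After treatment.** The Introduction says: "A post treatment visit will be conducted 4 weeks after the end of treatment". The follow-up section that comes directly after Visit 6 refers back to a post-treatment visit, but no visit in the schedule narrative has that title.

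**The concern.** The end of treatment is attached to three different visits: Visit 4 by the cessation sentence, Visit 5 by the treatment-visit heading combined with the 4-week spacing, and Visit 6 by its heading. At most one can be the end of a 12-week phase.

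Two things are at stake.

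- **Exposure.** The number that does not fit sits in the operative instruction to stop the drug. Staff who work by visit number would stop early.
- **Meaning of the Visit 6 measures.** The schedule narrative names CT at only two points, Visit 2 and Visit 6, and bronchial wall thickening on CT is a secondary outcome. The narrative also names quality-of-life reassessment at Visit 6. If that visit is the post-treatment one, an end-of-treatment label would present off-drug measurements as on-drug ones. An analysis plan can choose which visit to analyse. It cannot change when the drug was stopped or when the scan was done.

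**Working it through.** **Inputs, all from the protocol**

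- Visit 2 = week 0 of treatment (Randomisation Visit).
- Treatment lasts 12 weeks, once daily (Introduction, Patient Allocation, Randomisation Visit).
- Visits 3, 4 and 5 each follow a 4-week treatment period (Treatment Visits).
- Visits are monthly, with one visit 4 weeks after treatment ends (Introduction).
- There are at least six visits (Study Design).

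**Step 1: test the stated cessation visit.** Week of visit v = 4 × (v − 2). Daily doses by then = 7 × week. Study week counted from Visit 1 adds the 2-week run-in.

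| Visit | Treatment week | Doses due if treated to that visit | Week from Visit 1 |
|---|---|---|---|
| 2 | 0 | 0 | 2 |
| 3 | 4 | 28 | 6 |
| 4 | 8 | 56 | 10 |
| 5 | 12 | 84 | 14 |
| 6 | 16 | not applicable (see objection) | 18 |

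The protocol's pairing of Visit 4 with the end of 12 weeks is not reproduced. Visit 4 is week 8, and week 12 is Visit 5. The shortfall if drug stops at Visit 4 is (84 − 56)/84 = 1/3.

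**Step 2: look for a reading that rescues the label.** The spacing needed to put week 12 at visit v is 12/(v − 2):

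- Visit 4: 12/2 = 6 weeks.
- Visit 5: 12/3 = 4 weeks.
- Visit 6: 12/4 = 3 weeks.

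Only 4 weeks matches the stated spacing. Counting from Visit 1 puts Visit 4 at week 10, which is still not 12. Visit 4 would be week 12 if randomisation were numbered Visit 1, but the protocol numbers it Visit 2.

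**Step 3: place Visit 6.** The protocol prints no week for Visit 6. Continuing the monthly pattern gives week 16. The end of treatment plus 4 weeks gives 12 + 4 = 16. The two agree. The count agrees as well: one screening, one randomisation, three treatment and one post-treatment visit make six, the stated minimum. The back-reference in the follow-up section also points to Visit 6 as the post-treatment visit. Its heading says otherwise.

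**Step 4: consequences of following the Visit 4 label.** Drug stops at week 8. The visit 4 weeks later (8 + 4 = 12) is then Visit 5, which the protocol heads as a treatment visit. Visit 6 would be 16 − 8 = 8 weeks off drug. The Visit 4 label therefore conflicts with the stated duration, with the treatment-visit heading and with Visit 6 as the post-treatment visit.

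**The case against.** **It is a numbering slip.** This is the strongest reply, and much of it stands. Every statement of duration says 12 weeks, including the cessation sentence itself. The rest of the text largely shows how the visits fit together, and only one bracketed number and one heading are out of line. What remains is that the number sits in the instruction to stop the drug, and that the second label is the heading of the visit at which the follow-up CT is done.

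**The schedule table may settle it.** Appendix I is illegible in the copy reviewed and the design figure is not shown, so a correct visit-by-week table may exist. Its absence is not held against the plan. Even so, a correct table would contradict the narrative as it now reads.

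**Stronger readings that a reader might infer, and that the protocol does not support:**

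- *That treatment length is in dispute.* No section states any length other than 12 weeks. The dispute is over labels.
- *That participants could receive 16 weeks of drug.* This rests on the Visit 6 heading alone; the section beneath it says nothing about continuing or stopping drug. Patient Allocation has medication dispensed at each visit but ties no quantity to a visit number.
- *That the primary outcome loses power through washout.* The protocol gives no figure for how fast an IL-8 effect fades, so no loss can be calculated. Sputum is also collected at Visits 3 to 5, so a week-12 sample is scheduled whatever Visit 6 is called.
- *That the lack of a stated week for the IL-8 comparison is itself an error.* A statistical analysis plan commonly fixes this.

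**Quality of life may be measured at other visits.** The section on clinical history and symptom scores can be read as scheduling it at every visit from Visit 2. If so, the label affects that measure less. The narrative gives no such alternative for CT.

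**Conclusion.** The contradiction is real but limited to two labels. Visit 4 in the cessation instruction is week 8, not week 12. The Visit 6 heading marks as end of treatment a visit that the rest of the text places 4 weeks after it.

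If staff follow the visit number, exposure falls by 4 weeks, or one third. If they follow the 12-week duration, exposure is as planned, and the remaining fault is that the Visit 6 CT, quality-of-life and sputum measures are labelled end-of-treatment while taken 4 weeks off drug.

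This rests on three assumptions: randomisation at Visit 2 starts treatment, visits are spaced 4 weeks apart as stated, and Visit 6 continues that spacing. The first two are in the text. The third is inferred, but two separate statements lead to it. The conclusion does not depend on alpha, power, effect size or withdrawal rate. It is worth correcting because the instruction is operative and the correction costs almost nothing.

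**What to change.** Reconcile the Introduction, Patient Allocation, Randomisation Visit, Treatment Visits, End of Treatment Visit and Post Treatment Follow Up sections, so that each visit number has one study week and one on-drug or off-drug status. Correct the visit number or heading that does not fit. Check Appendix I and the design figure against the result.

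Then state whether the Visit 6 quality-of-life, CT and sputum measures are on-treatment or post-treatment, and use that description wherever these outcomes are reported.

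Which labels stand is for the investigator to decide; this review takes no position on the clinical schedule. The cost is a few words in the narrative and a consistency check. No visit, test or participant is added.

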#### End of Treatment Visit (Visit 6)

Symptom scores and quality of life scores will be reassessed. Spirometry, sputum analysis and blood parameters will be repeated. A high resolution CT scan of the chest will be formed to assess bronchial wall thickening.

#### Post Treatment Follow Up (Exacerbation visits and telephone consultations)

After the post treatment visit, participants will be contacted by telephone at least monthly and asked about their symptoms and medication use.

### *Clinical History and Symptom scores*

A standardised clinical history for respiratory symptoms will be taken. The medications the patient is currently taking will also be recorded. Quality of life scores will be assessed using the St George Respiratory questionnaire. Participants will also be questioned about potential side effects of azithromycin (AZM). This will be done on the second visit, when they are randomised to either placebo or AZM, then every visit thereafter and by phone every two weeks between visits. If during the phone contact there are concerns regarding potential toxicity the participant will be reviewed as soon, as is practicable. Individual symptoms will be recorded using visual analogue scales.

### *Pulmonary Function Tests and Sputum Induction*

A sputum induction will be performed as described elsewhere (12). The tests will use a KoKo K313100 spirometer (PDS Instrumentation, Inc. Louisville CO USA). Hypertonic saline (4.5% saline) will be nebulised using a De-Vilbiss ultrasonic nebuliser (Somerset, PA USA) and aerosol delivered via a one-way non-rebreathing Hans Rudolph valve box. Between testing the participant will be asked to expectorate sputum. Each participant will undergo a maximum of 16 minutes nebulisation time and nebulisation time within participants will be kept constant.

### *Sputum Analysis*

Sputum will be analysed as described elsewhere (12). It will be processed within 1 hour of collection. Muco-cellular clumps will be selected from the saliva. A total cell count and differential will be performed. Cytospin slides will be prepared for a differential cell count. Cytokine analysis on sputum supernatant will be performed with ELISA kits to detect IL-8 and NE. Measurements will be made with commercially available immunoassays according to manufacturers recommended protocols.

## **Appendix I: Study Schedule**

[illegible]

**Appendix II: Diary Card**

|                                                                             |                                                    |                                                           |   |                 |   |   |   |   |   |   |  |                 |   |   |   |   |   |   |  |
|-----------------------------------------------------------------------------|----------------------------------------------------|-----------------------------------------------------------|---|-----------------|---|---|---|---|---|---|--|-----------------|---|---|---|---|---|---|--|
| SYMPTOM SEVERITY SCORE:                                              |                                                    | 0 = absent, none at all    2 = Moderate Discomfort |   |                 |   |   |   |   |   |   |  |                 |   |   |   |   |   |   |  |
|                                                                             |                                                    | 1 = Mild Discomfort        3 = Severe Discomfort   |   |                 |   |   |   |   |   |   |  |                 |   |   |   |   |   |   |  |
| NAME:                                                                       |                                                    | Example                                                   |   | Week Commencing |   |   |   |   |   |   |  | Week Commencing |   |   |   |   |   |   |  |
| 1. During the previous 24hrs                                         |                                                    | M                                                         | T | M               | T | W | T | F | S | S |  | M               | T | W | T | F | S | S |  |
|                                                                             | Cough (0-3)                                        |                                                           |   |                 |   |   |   |   |   |   |  |                 |   |   |   |   |   |   |  |
|                                                                             | Wheeze (0-3)                                       |                                                           |   |                 |   |   |   |   |   |   |  |                 |   |   |   |   |   |   |  |
|                                                                             | Shortness of Breath (0-3)                          |                                                           |   |                 |   |   |   |   |   |   |  |                 |   |   |   |   |   |   |  |
|                                                                             | Times woken last night due to chest ?              |                                                           |   |                 |   |   |   |   |   |   |  |                 |   |   |   |   |   |   |  |
|                                                                             | Where your activities limited today due to chest ? |                                                           |   |                 |   |   |   |   |   |   |  |                 |   |   |   |   |   |   |  |
|                                                                             | Number of puffs of Reliever Medication?            |                                                           |   |                 |   |   |   |   |   |   |  |                 |   |   |   |   |   |   |  |
|                                                                             | Did you take your Study Medication (Y/N)           |                                                           |   |                 |   |   |   |   |   |   |  |                 |   |   |   |   |   |   |  |
| COMMENTS: _____                                                      |                                                    |                                                           |   |                 |   |   |   |   |   |   |  |                 |   |   |   |   |   |   |  |
| _____                                                                       |                                                    |                                                           |   |                 |   |   |   |   |   |   |  |                 |   |   |   |   |   |   |  |
| If you have any further questions about the study or the diary please phone |                                                    |                                                           |   |                 |   |   |   |   |   |   |  |                 |   |   |   |   |   |   |  |
